# LIST OF ABBREVIATIONS

| ACPR | Adequate Clinical and Parasitological Response |
| --- | --- |
| ACT | Artemisinin-based combination chemotherapy |
| AE | Adverse Event |
| ALT | Alanine aminotransferase |
| BP | Blood Pressure |
| CI | Confidence Interval |
| CRF | Case Report Form |
| CRO | Clinical Research Organization |
| ECG | Electrocardiogram |
| EDTA | Ethylenediaminetetraacetic Acid |
| ETF | Early Treatment Failure |
| FCT | Fever Clearance Time |
| GCP | Good Clinical Practice |
| GLP | Good Laboratory Practice |
| GMP | Good Manufacturing Practice |
| h | Hour |
| Hb | Haemoglobin |
| ICH | International Conference on Harmonization |
| IEC | Independent Ethics Committee |
| IRB | Institutional Review Board |
| ITT | Intention to treat |
| IU | International Unit |
| LCF | Late Clinical Failure |
| LPF | Late Parasitological Failure |
| MMV | Medicines for Malaria Venture |
| mg | Milligram |
| NA | Not Applicable |
| PCR | Polymerase Chain Reaction |
| PCT | Parasite Clearance Time |
| PP | Per Protocol |
| RBC | Red Blood Cells |
| R&D | Research and development |
| SAE | Serious Adverse Event |
| SAS | Statistical Analysis System |
| SP | Sulfadoxine-pyrimethamine |
| TDR | Tropical Disease Research |
| TF | Treatment Failure |
| URTI | Upper Respiratory Tract Infection |
| WBC | White Blood Cells |
| WHO | World Health Organization |

# ABSTRACT

Artekin is an artemisinin-based fixed-dose antimalarial drug combination developed in the 1990s in China. The active components are dihydroartemisinin and piperaquine. Piperaquine is a bisquinoline compound originally synthesized in France with high *in vitro* activity in the nanomolar range against multidrug resistant *Plasmodium falciparum*. Piperaquine has been used as monotherapy in China for over two decades. It has proved to be generally very well tolerated and effective although resistance to the monotherapy has developed until the early 1990s prompting its reformulation in combination with other drugs, including dihydroartemisinin. Dihydroartemisinin has already been extensively evaluated and shown to be safe – with no major identifiable adverse effects. The combination has become widely used in South East Asia and is now registered in Cambodia, China and Vietnam.

Several factors make this combination a promising development: Artekin is a fixed-dose co-formulation used as a once daily 3-day regimen, and this may improve adherence and ease of drug administration in comparison for instance to the more complex regimens of artemether-lumefantrine (Coartem©). It is also inexpensive in comparison with other artemisinin-based combination chemotherapies, e.g. Coartem© or artesunate-mefloquine with an estimated cost per adult treatment of approximately 1 USD. Finally, preliminary clinical trials of this treatment in more than 5,000 patients carried out in South East Asia have shown it to be well tolerated and highly effective on par with Coartem© and artesunate-mefloquine in areas of high-level multi-drug resistance of *P. falciparum*.

This study is part of a multicentre phase III trial aimed at evaluating the safety and efficacy of the newly manufactured GMP batch of Artekin in 1,500 African children with uncomplicated *P. falciparum* malaria. In Kilifi, 500 patients aged 6-59 months with uncomplicated *P. falciparum* malaria will be randomly allocated to receive either dihydroartemisinin-piperaquine or artemether-lumefantrine. The objective of the study is to evaluate the efficacy and safety of dihydroartemisinin-piperaquine and to demonstrate that dihydroartemisinin-piperaquine (1) is at least as effective as artemether-lumefantrine and (2) cures at least 90% of treated patients.

# INTRODUCTION/BACKGROUND

It is generally acknowledged that artemisinin-based combination therapies (ACTs) currently provide the best available treatment option for uncomplicated *P. falciparum* malaria [1]. They give fast therapeutic responses, provide high cure ratios with a short duration of treatment, reduce gametocyte carriage, provide mutual protection against the emergence of resistance, and they are well tolerated. On the north-western border of Thailand, which harbours some of the most multi-drug resistant *P. falciparum* strains in the world, the widespread use of ACTs since 1994 has led to a sustained reduction in the incidence of *P.* *falciparum* malaria, and a hitherto unseen reversal of mefloquine *in vitro* resistance [2]. One of the main obstacles to more widespread adaptation of the use of ACTs in malaria endemic areas has been cost. The two currently available ACTs, artesunate-mefloquine and artemether-lumefantrine, cost USD 3 and USD 2.4, respectively per adult treatment course (expensive for majority of patients or national health services in most endemic countries). Projected costs for other ACTs, which are not yet available, are similar (artesunate-pyronaridine) or even higher (artesunate-atovaquone-proguanil). Furthermore mefloquine is associated with nausea, dizziness, and dysphoria, and has not been adopted in African countries because of high variability in absorption rates, and thus, efficacy concerns in children. Artemether-lumefantrine is very well tolerated but needs to be given twice daily, and lumefantrine has poor oral bioavailability in the if not concurrently taken with fatty food. Chlorproguanil-dapsone-artesunate (CDA) is a possible option that may be relatively inexpensive, but has not yet undergone clinical trials (currently still in phase II). There is also some concern that, by the time CDA is registered, continued widespread use of sulphadoxine-pyrimethamine would have already selected for highly antifolate resistant parasites. Artesunate-amodiaquine is also relatively inexpensive, but is not co-formulated yet, and already has reduced efficacy in Africa because of rapidly emerging parasite resistance to amodiaquine.

The combination of dihydroartemisinin and piperaquine was originally developed in the 1980s in China. Dihydroartemisinin-piperaquine has been extensively evaluated in clinical trials in Thailand, Vietnam, Cambodia, and China [3-6]. Efficacy has been high and tolerability uniformly excellent in all trials in these multi-drug resistant areas including Cambodia and Vietnam [4, 5]. These trials have used a constant dose of piperaquine, but initially the co-formulation also included trimethoprim (CV8). This formulation (CV8) has been used extensively in Vietnam, where it is part of national antimalarial treatment policy. More recently the dose of dihydroartemisinin in dihydroartemisinin-piperaquine has been increased by 25%. This product (Artekin) has been registered in China, Cambodia and Vietnam. The fixed-dose combination dihydroartemisinin-piperaquine will cost approximately USD 1.2 or less for an adult treatment course given over 48 hours (similar to CDA or artesunate-amodiaquine).

Piperaquine is an orally active bisquinoline discovered by Rhone-Poulenc in the early 1960s and developed for clinical use in China in 1973 [7-9]. The phosphate salt is water-soluble. *In vitro* testing in several laboratories has shown that piperaquine is approximately equivalent to chloroquine against sensitive parasites and significantly more effective than chloroquine against chloroquine-resistant *P. falciparum* strains*.* Like other members of this class of antimalarials piperaquine chemically is thought to inhibit bio-crystallisation of haem in the food vacuole of the parasite. The estimated terminal elimination half-life is approximately 14 days in children with uncomplicated *P. falciparum* [10-12].

The gastrointestinal side effects of piperaquine are similar to those of chloroquine but milder at total doses of less than 2 g. In any other aspect the toxicity profiles are similar. Piperaquine replaced chloroquine as recommended treatment for *P.* *falciparum* malaria in China in 1978. Over the next 14 years 214 tons of piperaquine phosphate equivalent to 140,000,000 adult doses, were used for mass prophylaxis and treatment. Thus, in terms of drug treatment administered, piperaquine is amongst the most widely used antimalarial drugs in the world. Surveillance at the time found no adverse events other than rare cases of rash.

Dihydroartemisinin is the active metabolite of artesunate and artemether, and manufactured as an oral antimalarial drug in its own right China [13]. It has equivalent clinical efficacy to the more widely used artesunate. The mode of antimalarial action of this class of compounds is thought to involve intraparasitic Fe++ catalysed production of carbon centred free radicals.

Dihydroartemisinin is absorbed and eliminated rapidly (t1/2 circa 45 min in adult patients with uncomplicated *P. falciparum* malaria) [14]. To date no significant resistance to the artemisinin class of antimalarials has been reported and stable resistance cannot be induced in the laboratory. These drugs are safe in clinical use; there is no evidence that they produce neurotoxicity [15]. The only confirmed reports of adverse effects concern rare idiosynchratic type 1 hypersensitivity reactions [16]. There is overwhelming evidence of selected brainstem neurotoxicity from animal experiments, especially with oil-soluble artemisinin derivatives and a recent report of irreversible hearing loss after treatment with artemether-lumefantrine is of concern. However, detailed neurological examinations including pure-tone audiometry and auditory-evoked brain stem responses (ABR) failed to detect significant differences between mostly adult patients orally treated with either artesunate or artemether and age- and sex-matched controls [17]. A post-mortem comparative study of adult patients treated with either quinine or artemether for severe malaria was also negative with regard to any histopathological correlates of neuronal damages [18]. In experimental animals with early pregnancies fetal toxicity leading usually to fetal resorption occurs with high doses of the artemisinin derivatives. Clinical experience in pregnancy to date, however, has shown no cause for concern [19]. A recent WHO consensus committee concluded these drugs could be used in the second and third trimesters, but pending further information, not in the first trimester of pregnancy [20].

Dihydroartemisinin-piperaquine is co-formulated as a film tablet containing 40 mg of dihydroartemisinin and 320 mg of piperaquine phosphate for oral treatment of uncomplicated *P. falciparum* malaria. Dose finding studies in Thailand and Vietnam established the excellent safety and high efficacy of a once daily 3-day regimen of dihydroartemisinin at 4 mg/kg/day [21]. These phase II-type studies were conducted with the currently available non-GMP formulation in the expectation that oral bioavailability of the new GMP formulation will be similar. We will use the new GMP formulation provided by SigmaTau (Italy) in this study. Our study will be part of a phase III multicentre trial involving five studies sites in five African countries.

Piperaquine has a long terminal elimination half-life of approximately 14 days [11]. This might favour an accelerated emergence and spread of resistant parasite alleles, but by acting as a selective filter at time of reinfection [22].

Dihydroartemisinin-piperaquine is an ACT that seems to offer a highly efficacious, safe, well tolerated, simple and affordable treatment option for uncomplicated *P. falciparum* malaria in endemic countries.

# JUSTIFICATION FOR THIS STUDY

The inexorable spread of resistance of the malaria parasite *P. falciparum* to affordable antimalarial drugs such as chloroquine and sulfadoxine-pyrimethamine causes a public health crisis in sub-Saharan Africa. In the absence of a registered and effective malaria vaccine in the foreseeable future, antimalarial chemotherapy has to be improved dramatically to replace the currently used antimalarials. WHO currently advocates the use of artemisinin-based combination chemotherapy with prompt antiparasitic action and mutual protection against parasite resistance for the treatment of malaria [23, 24]. At present, the only fixed-dose combination registered up to international standards is artemether-lumefantrine (Coartem®), but artemether-lumefantrine has a rather complex treatment regimen requiring a total of six doses administered twice daily over three days, and the price is high (USD 2.4 under special agreements between the manufacturer and WHO). Other fixed-dose artemisinin-based combinations are under development (artesunate-amodiaquine, or chlorproguanil-dapsone-artesunate) but their future use might be compromised by existing cross-resistance to currently used antimalarial drugs (chloroquine and sulfadoxine-pyrimethamine). Dihydroartemisinin-piperaquine is a promising alternative, which has been shown very safe in more than 5,000 treated patients and proved to be highly effective in areas of multi-drug resistance. A fixed-dose co-formulation of dihydroartemisinin-piperaquine (Artekin) is currently developed according to international standards as a once daily 3-day regimen, which is likely to improve adherence and to increase effectiveness. It is comparably inexpensive costing approximately 1 USD per adult treatment. If proved to be safe and efficacious, dihydroartemisinin-piperaquine will be an important addition to the currently available treatment options for uncomplicated childhood malaria due to multidrug-resistant *P. falciparum* in Kenya.

# NULL HYPOTHESIS

Dihydroartemisinin-piperaquine is non-inferior to artemether-lumefantrine in the treatment of paediatric patients aged 6 to 59 months with uncomplicated *P. falciparum* malaria as assessed by clinical and parasitological cure on day 28.

# OBJECTIVES

## Primary objectives:

The primary objective of the study is to measure the day 28, PCR-corrected cure ratios of dihydroartemisinin-piperaquine and artemether-lumefantrine and demonstrate that:

- The cure ratio of dihydroartemisinin-piperaquine is non-inferior to that of artemether-lumefantrine (non-inferiority margin = 5%);
- The cure ratio of dihydroartemisinin-piperaquine is at least 90%.

This cure ratio is defined as the proportion of evaluable patients with adequate clinical and parasitological response at day 28.

## Secondary objectives:

- PCR-uncorrected day 28 cure ratio;
- Safety profiles of the two treatments;
- Time to asexual parasite clearance (PCT);
- Time to fever clearance (FCT);
- Gametocyte prevalence and density on days 7, 14, 28, 42, 63 and 84;
- Haematological recovery (Haemoglobin (Hb) changes from day 0 to day 28, day 42, and day 84;
- Cure ratios at day 42 (PCR corrected and PCR uncorrected);
- Cure ratios at day 63 (PCR corrected and PCR uncorrected);
- Cure ratios at day 84 (PCR corrected and PCR uncorrected);
- Rate of PCR-confirmed reinfections to estimate the chemoprophylactic effect of dihydroartemisinin-piperaquine;
- Plasma concentration of piperaquine at time of asexual parasite reappearance;
- Detection of subpatent asexual parasitaemia on day 7 **and day 14;**
- **Assessment of the relationship between *var* gene transcription patterns and late asexual parasite recurrence**

# DESIGN AND METHODOLOGY

## Study site

The study will be conducted at the new Pingilikani study site, which is being extensively upgraded as an extension of the outpatient department (OPD) clinic at KEMRI Centre for Geographic Medicine Research-Coast (CGMR-C). The Pingilikani study site is located 20 km south of Kilifi town in Kilifi district along the Kenyan coastal region. It lies within the censused area of the Demographic Surveillance System operated by CGMR-C in Kilifi District. Good Clinical Practice will be implemented and adequately monitored. Severely-ill patents requiring hospitalisation can be transferred to Kilifi District Hospital at any times, day and night.

## Study design

This study is part of a phase III, randomized, open label, two-armed study involving 5 study centres, which will enroll a total 1,500 patients (1,000 dihydroartemisinin-piperaquine; 500 artemether-lumefantrine). Each study will enroll 300 patients into the multicentre study protocol (the other study sites are in Mozambique, Burkina Faso, Uganda, Zambia). In addition, 200 additional patients will be enrolled in the KEMRI study (1) to allow an independent statistical analysis of the KEMRI study and (2) to increase the precision of the estimated chemoprophylactic effect of dihydroartemisinin-piperaquine. Patients enrolled in the KEMRI study will also be followed up for a longer period until day 84 (instead of day 42). These changes will in effect act as an amendment to the multicentre study protocol and will not interfere with the analysis of the multicentre protocol. The data from the first 300 patients (day 0 - day 42) will be fully compatible with the multicentre protocol.

## Study populations

### Inclusion criteria

In order to be eligible, patients should satisfy the following inclusion criteria:

1. Males and Females aged between 6 months and 59 months inclusive.
2. Body weight of 5 Kg and above.
3. Microscopically confirmed, monoinfection of *Plasmodium falciparum* (parasitaemia ≥ 2,000/μL to 200,000/μL).
4. History of fever in the previous 24 hours or presence of fever (axillary temperature at ≥ 37.5°C).
5. Signed informed consent by the parents or guardians.
6. Parents’ or guardians’ willingness and ability to comply with the study protocol for the duration of the trial.

### Exclusion criteria

1. Participation in any investigational drug study during the previous 30 days.
2. Known hypersensitivity to the study drugs.
3. Severe malaria.
4. Danger signs: not able to drink or breast-feed, vomiting (>twice in 24 hours), recent history of convulsions (>1 in 24h), unconscious state, unable to sit or stand.
5. ECG abnormality that requires urgent management.
6. Presence of intercurrent illness or any condition which in the judgment of the investigator would place the subject at undue risk or interfere with the results of the study.
7. Severe malnutrition (defined as weight for height <70% of the median NCHS/WHO reference).

## Outcome measures and sample size.

### End points

#### Primary end point

The primary end point will be the PCR-corrected adequate clinical and parasitological response (PCR corrected ACPR) at day 28.

ACPR is defined as the absence of parasitaemia on day 28 irrespective of the axillary temperature without previously meeting any of the criteria of early treatment failure or late clinical or parasitological failure.

Patients with late asexual parasite reappearance will be considered ACPR if the PCR analysis shows a new infection rather than a recrudescence.

The total treatment failure is defined according to the WHO criteria [25] as the sum of early and late treatment failures (for definitions see chapter 7.3 Treatment failure).

#### Secondary end points

The secondary end points will be:

1. Crude (PCR uncorrected) adequate clinical and parasitological response ratio at day 28 (PCR-uncorrected ACPR)
2. Cure ratios at days 42, 63, and 84 (PCR-corrected and PCR-uncorrected ACPR)
3. Fever clearance time (FCT)

Fever clearance time will be defined as the time (in hours) from the start of a patient’s treatment to the first consecutive axillary temperature measurements below 37.5°C (body temperature <37.5ºC for at least 48 hours).

1. Asexual parasite clearance time (PCT)

Asexual parasite clearance time will be defined as the time (in days) from the start of a patient’s treatment to 2 consecutive negative blood slides (collected at different days).

1. Gametocyte carrier rates and geometric mean densities (excluding negatives) will be compared on days 7, 14, 28 and 42.
2. Changes of haemoglobin (Hb) concentration from day 0 to days 28, 42, 63, and 84.
3. Safety profiles of the two treatments.
4. Adverse events, vital signs, blood chemistry and haematology, electrocardiogram (ECG) will be monitored and changes in relevant laboratory parameters will be assessed.
5. Rate of PCR-confirmed reinfections
6. Plasma concentration of piperaquine at time of asexual parasite reappearance.
7. Detection of subpatent asexual parasitaemia on day 7 **and day 14**
8. **Assessment of the relationship between *var* gene transcription patterns and late asexual parasite recurrence**

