### Sample size calculation

The study is designed as a non-inferiority trial.

The opinion of physicians and experts in malaria treatment has been sought for defining the non-inferiority margin, and this has been set at 5%. In addition, the experts have agreed that, in order for the new treatment to be considered efficacious, its PCR-corrected cure ratio at day 28 should not be lower than 90%. Therefore, in the present trial, dihydroartemisinin-piperaquine will be considered efficacious if both the following conditions are met (see section 2.1):

(i) The PCR-corrected cure ratio at day 28 of dihydroartemisinin-piperaquine is not inferior to the cure rate of artemether-lumefantrine by 5% or more, and independently of the reference drug performance,

(ii) The cure rate of dihydroartemisinin-piperaquine is at least 90%.

In summary, for the non-inferiority analysis, the clinical and statistical specifications for the sample size computations are as follows:

- Primary end point = PCR-corrected cure ratio at day 28.
- Primary analysis = based on 97.5% one-sided confidence intervals for the difference in day 28 cure ratios.
- Alpha = 0.025 (one-sided).
- Power = 80%.
- Cure ratio at day 28 of artemether-lumefantrine = 95% (results from multicentre phase III trial of Coartem in children; [name] personal communication).
- Non-inferiority margin for the difference (test-reference) = -0.05%.
- Analysis will be per-protocol.

To demonstrate non-inferiority of Artekin compared to Coartem the study will require 235 patients per treatment group. To allow for an approximate 5% loss to follow-up rate, 250 patients per treatment group (500 patients in total) will be enrolled in the Kilifi study.

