1. PCR

A blood sample will be collected on filter paper (grade 1) for parasite genotyping.

1. Blood Slide

A thick and thin blood smear will be obtained from the subject to verify the presence of *P. falciparum* and to determine asexual and sexual parasite densities. Thick and thin blood films will be prepared, dried and stained with Giemsa stain according to standard operating procedures.

Parasite density will be calculated by counting the number of asexual parasites per 200 leukocytes in the thick blood film, based on an assumed leukocyte count of 8,000 /µl by light microscopy at 1000x magnification. One hundred high-powered fields (HPF) will examined (independent of presence or absence of asexual parasite stages). The parasite density per µL will be calculated using the following formula: numbers of parasites/µl = number of parasites counted x 8,000/number of leukocytes counted

1. Laboratory Tests

Blood haemoglobin, red blood cell count, total leukocyte count, differential count (neutrophils, basophils, eosinophils, monocytes, lymphocytes) and platelet count.

Total bilirubin, ALT and creatinine will be measured. **Parasite RNA will be analysed for variant gene expression patterns.**

1. Administration of the study drugs

For details see chapter 7 (Investigational product(s) & concomitant medications and non-drug therapies).

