### Secondary end point analyses

#### Secondary efficacy end point analyses

Normally distributed variables will be summarized by calculating means and standard deviations (SD) and compared with parametric tests (unpaired and paired Student’s *t* or analysis-of-variance (ANOVA) tests as appropriate). Non-normally distributed variables will be summarized by median and interquartile ranges (IQR) or geometric means and 95% confidence intervals. Comparisons will be made with nonparametric tests (unpaired and paired Wilcoxon or Kruskal-Wallis rank tests as appropriate). The Fisher’s exact test will be used to assess differences in categorical outcome variables between the cohorts. The statistical significance level will be set to 5%.

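### Gametocyte carriage is compared without the day 0 reading, which gives up precision, and density only among children positive at the visit, which is not a randomised comparison

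*Protocol*

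**What the plan says.** The Protocol's secondary end points (10.4.1.2) state: "Gametocyte carrier rates and geometric mean densities (excluding negatives) will be compared on days 7, 14, 28 and 42". Day 0 is not on that list, and the density part is limited to children with gametocytes seen at the visit. The secondary objectives (9.2) give a longer list of days: "Gametocyte prevalence and density on days 7, 14, 28, 42, 63 and 84". They also leave out day 0, and they do not mention dropping negatives.

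The day 0 visit (10.5.1.1) has a blood film read "to determine asexual and sexual parasite densities", so each child has a baseline gametocyte value.

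Section 12.3.2.1 sets the tests for secondary efficacy end points. For categorical outcomes Fisher's "exact test will be used to assess differences in categorical outcome variables between the cohorts". For variables that are not normally distributed: "Comparisons will be made with nonparametric tests (unpaired and paired Wilcoxon or Kruskal-Wallis rank tests as appropriate". No covariate or stratification factor is named. In the same list of end points haemoglobin does use its baseline: "Changes of haemoglobin (Hb) concentration from day 0 to days 28, 42, 63, and 84".

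**The concern.** There are two separate issues.

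**Carriage.** Children who carry gametocytes at entry may supply a good part of the carriage seen soon after treatment. If so, day 0 status explains much of the variation between children. A test that ignores it has less power than one using a value the trial already holds.

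**Density.** Whether a child is positive on day 7, 14, 28 or 42 is itself an outcome that treatment can change. Comparing density only among positives compares two groups that treatment may have selected differently, so randomisation no longer protects the comparison. A drug that mainly removes or prevents low-density carriage leaves the denser carriers in the average. It can then show the higher mean density while fewer children carry gametocytes.

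Both arms are artemisinin combinations, and the introduction counts reduced gametocyte carriage among the benefits of that class. The comparison is likely to be read as evidence on that benefit.

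**Working it through.** **Inputs.** From the Protocol: 250 children enrolled per group and 235 evaluable (10.4.2); a 5% significance level for secondary end points, taken as two-sided (12.3.2.1); density = parasites counted × 8,000 / leukocytes counted, over 200 leukocytes (10.5.1.1). There is no gametocyte power statement to reproduce and no carriage rate, so all carriage rates and densities below are assumptions.

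**Step 1: carriage, closed form.** In day 0 stratum s let n_s be the children per arm, d_s the difference in follow-up carriage between arms, and m_s the mean of the two arms' rates. The Mantel-Haenszel statistic has

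- U = Σ (n_s/2) d_s
- V = Σ (n_s/2) m_s(1 − m_s) · 2n_s/(2n_s − 1)
- power ≈ Φ(U/√V − 1.96)

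The unadjusted score test is the same with one stratum.

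Example: 250 per arm; 20% carriers on day 0; follow-up carriage 50% in day 0 carriers and 10% in others; odds ratio 2 within strata, which gives 66.7% and 18.2% in the other arm. Overall carriage is 18.0% versus 27.9%.

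- Unadjusted: U = 125 × 0.0988 = 12.35; V = 125 × 0.2294 × 0.7706 × 500/499 = 22.14; U/√V = 2.62; power Φ(0.66) = 75%.
- Stratified: U = 25 × 0.1667 + 100 × 0.0818 = 12.35; V = 25 × 0.5833 × 0.4167 × 100/99 + 100 × 0.1409 × 0.8591 × 400/399 = 18.27; U/√V = 2.89; power Φ(0.93) = 82%.

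The numerator is the same and the variance is smaller. That is the whole gain.

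**Step 2: carriage, simulation, with Fisher's test added.**

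| Per arm | Day 0 carriage | Follow-up carriage if day 0 positive / negative | Odds ratio | Fisher | Unadjusted score | Stratified | Gain over score |
|---|---|---|---|---|---|---|---|
| 250 | 20% | 50% / 10% | 2.0 | 72% | 76% | 83% | 7 |
| 250 | 20% | 70% / 8% | 2.0 | 49% | 54% | 75% | 21 |
| 250 | 20% | 35% / 12% | 1.9 | 74% | 77% | 80% | 3 |
| 235 | 15% | 60% / 5% | 2.0 | 39% | 44% | 60% | about 16 |
| 235 | 15% | 20% / 10% | 2.0 | 72% | 76% | 77% | under 1 |

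The closed form gives, for score and stratified in the same order, 75 and 82, 54 and 73, 77 and 80, 43 and 59, and 75 and 76%, so it agrees within about 2 points. With no treatment effect the stratified test rejected in 4.2% to 5.5% of trials and Fisher's test in 2.8% to 4.3%.

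**Step 3: density, a case where the order reverses.** Take 235 per arm. Each arm has 20 carriers at 160/µL. The better drug has 5 further carriers at 40/µL and the worse drug has 40.

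- Carriage: 25/235 = 10.6% versus 60/235 = 25.5%.
- Positives-only geometric mean: 160^(20/25) × 40^(5/25) = 121/µL versus 160^(20/60) × 40^(40/60) = 63/µL. The worse drug looks better.
- All children, exp(mean of log(density + 1)) − 1: exp[(20 ln 161 + 5 ln 41)/235] − 1 = 0.67 versus exp[(20 ln 161 + 40 ln 41)/235] − 1 = 1.90. The order is right.

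A milder case: 20% carriers, log-normal density with median 60/µL and log SD 1.2; 20% or 70% of carriers below 60/µL cleared and 10% of those above; detection limit 1 × 8,000/200 = 40/µL. The share of carriers between 40 and 60/µL is 0.500 − 0.368 = 0.132, with geometric mean 49/µL; above 60/µL it is 0.5, with geometric mean 156/µL.

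- Carriage: 0.2 × (0.132 × 0.8 + 0.45) = 11.1% versus 0.2 × (0.132 × 0.3 + 0.45) = 9.8%.
- Positives-only geometric mean: 125 versus 142/µL.

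**Step 4: density, a case where the order is kept.** Shift the whole log10 density distribution (SD 1, mean 0, 0.3 or 0.6, same limit). Carriage is 5.5%, 9.6% and 15.8%, and the positives-only mean is 106, 118 and 134/µL. Both rise together.

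**The case against.** A randomised trial needs no baseline adjustment for a valid test, and covariates for one secondary end point are often left to the analysis plan, which is not at hand. A geometric mean cannot contain zeros, so excluding negatives partly just defines the statistic. The carrier rate stands beside it, where a reader would see both.

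Much of this stands, and it rules out several stronger readings that a reader might infer:

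- *That the carriage test is wrong or biased.* It is not. Only precision is lost, and how much depends on rates the protocol does not give.
- *That the whole gap between Fisher's test and the stratified test is due to day 0.* Part is the conservatism of Fisher's test. In the third row of the table 3 of the 6 points come from day 0.
- *That the density group consists of children the drug failed to clear.* Children negative on day 0 who become carriers later are counted too.
- *That the density result will favour the worse drug.* Step 4 shows that it need not. The reversals in step 3 are constructed, and the 40/µL limit borrows a counting rule written for asexual parasites. In the milder case the difference reached significance in the misleading direction in about 9% of simulated trials, against 2.5% by chance.

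An all-children density test is no cure-all either. With about 90% zeros it largely repeats the carriage test, and in the milder case its power was only 6% to 7%.

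What the objection does not remove is that the protocol goes beyond silence. It writes down the restriction to positives, a between-arm comparison on that group, and unadjusted tests. An analysis plan would have to change these choices rather than fill a gap.

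**Conclusion.** The point holds in a limited form.

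The unadjusted carriage comparison is valid but less precise than it could be at no cost. Under the assumed rates, stratifying by day 0 carriage adds about 3 to 21 points of power over an unadjusted score test when day 0 status is moderately to strongly prognostic. It adds almost nothing when day 0 status is weak (20% versus 10%). At 333 and 167 per arm, the multicentre study's two-to-one ratio, the gain with a prognostic day 0 status is similar, about 4 to 18 points. The gain is probably largest on day 7 and smaller later, as entry carriage fades.

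The density comparison conditions on a state reached after randomisation. It is therefore not a randomised comparison and can, though need not, contradict the carriage result. How often it would do so cannot be determined from the protocol.

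This concerns one secondary end point and does not touch the primary conclusion. It should be changed, but it is not critical.

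**What to change.** In 10.4.1.2 and 12.3.2.1:

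- Compare carriage at each listed day with a Mantel-Haenszel test stratified by day 0 gametocyte carriage (yes/no), or a logistic model adjusted for it.
- Report the positives-only geometric mean beside the carrier rate as description, without a between-arm test.
- If density is to be tested, test it over all randomised children with negatives as zero (ranks, or log(density + 1) adjusted for day 0). State that with most values zero the result largely reflects carriage.
- In the same edit, make the days in 9.2 and 10.4.1.2 agree, since only the former includes days 63 and 84.

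The cost is wording only, because the day 0 film is already read. The small downside is that a density measure including zeros is less familiar to readers.
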